***Exercise counseling***

Counseling consists of 7 steps, as previously reported [19]: motivation, self-efficacy, pleasure, support, comprehension, lack of impediments, diary.

**Measurements**

***Assessment of physical fitness***

Parameters of physical fitness, i.e. cardio-respiratory fitness, strength and flexibility, will be evaluated at baseline and at the end of the study by the estimation of VO2max, a 5-8 maximal repetition (MR) and a standard bending, respectively. In the EXE Group, measurements will be performed also during the study period, in order to adjust the training loads according to improvements in fitness parameters.

*Cardio-respiratory fitness.* Assessment of cardio-respiratory fitness will consist of a sub-maximal VO2max evaluation, i.e. at 80% of the predicted maximal heart rate (MHR = 220 – age). It has been preferred to a maximal test, because (a) the latter cannot be performed without a cardiologist, according to the Italian law; (b) heart rate varies linearly with VO2 to the point of maximum exertion, thus allowing extrapolation of the actual VO2max value. The test will be preceded by two consecutive run-in sessions to become familiar with testing devices and protocols, based on the results of a pilot study showing that tests executed during the first visit have a very low reliability, which increases significantly with tests executed at the third visit. All patients will perform the test at the treadmill, which has been preferred to the cyclo-ergometer to avoid early muscle exhaustion in untrained subjects, using a protocol modified form the Balke and Ware procedure [22] (Table 6), with direct oxygen consumption analysis and concurrent assessment of heart rate. According to our protocol, patients will walk two minutes at the speed of 4.3 Km/hour at 0 % gradient (warm-up), wearing the mask of a gas exchange analyzer FitMate. Then, protocol will proceed automatically through the steps indicated in Table 5 and terminate when the patient reaches the 80% of the predicted MHR and the metabolic fitness instructor stops the procedure using the dedicated key function on the gas analyzer. In the case of patients taking medications that affect heart rate, such as -adrenergic blockers, the Borg Rate of Perceived Exertion scale will be used (version 1-10). Patients will be stopped at the perceived value of 5-6 (hard) because, according to ACSM’s guidelines, this value corresponds to a heart rate of 70-89%. Test duration will range from 5 to 15 minutes. In the EXE group, this protocol will be repeated every three months with the same modalities and monthly without direct readings of oxygen consumption, in order to adjust the training load throughout the exercise period. For every step exceeding the previous evaluation, the predicted VO2max will be incremented of 2 ml of oxygen and the training load will be increased accordingly.

*Strength.* For strength assessment, a RM test will be performed with the following modalities: thrust movement on the transverse plane (chest press or equivalent), traction movement on the frontal plane (lateral pull down or equivalent), and squat movement (leg press or equivalent). The 1RM test is the most reliable test for evaluating the maximal dynamic strength of a muscle or group of muscles. However, due the very low fitness profile of patients enrolled in this study, a MR test (or 5-8 RM test) has been preferred, for safety (to avoid maximal loads to the joint structures) and validity (untrained subjects are not always able to properly reach their 1RM) reasons. One RM will be then predicted from the weight loaded and the number of repetitions executed after a proper warm up using the Brzycki formula [23]. Results will be expressed as upper body (average of thrust movement and lateral pull down) and lower (leg press) body strength. In the EXE group, the MR test (with 5-8 repetitions) will be repeated every three months with the same testing machine to adjust the training load throughout the exercise period.

*Flexibility.* For hip and trunk flexibility assessment, a standard bending test will be executed. Standing on a step with legs fully extended, patients will be asked to bend the torso forward to try to touch the ground with their fingertips. The test will be performed three times and the distance between the finger and the ground will be measured by the exercise specialist at the third attempt.

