***Secondary outcomes***

Secondary research goals include an exploration of :

- Percentage of patients in each group that after 12 month achieve one or more of the following targets: HbA1c <6.5% or HbA1c reduction >0.5%; total cholesterol <175 mg/dl; LDL cholesterol <100 mg/dl; HDL cholesterol >40 mg/dl; triglycerides <150 mg/dl; systolic blood pressure (BP) <130 mmHg; diastolic BP <80 mmHg; BMI reduction >1; waist circumference reduction >5 cm.
- Difference between groups in terms of reduction of HbA1c, serum triglyceride and LDL-cholesterol, systolic and diastolic BP, BMI and waist circumference and increment of serum HDL-cholesterol.
- Difference between groups in terms of reduction of number and/or dosage of glucose-, lipid- and BP-lowering drugs.
- Difference between groups in terms of reduction of global cardiovascular 10-year risk (UKPDS risk engine tables).
- Difference between groups in terms of improvement of well-being.
- Difference between groups in terms of direct medical costs and direct and indirect social costs.
- Dose/response relationship between the quality (volume and intensity) of exercise training and modifiable cardiovascular risk factors.
- Relationship between physical fitness at baseline and during the study and modifiable cardiovascular risk factors.

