# On the third visit (R3), basal anthropometric and blood pressure (BP) measurements will be obtained and registered in the database, together with results of laboratory tests performed centrally. Subsequently all patients will receive a treatment regimen aimed at achieving optimal glycemic, lipid, BP and body weight targets, as established by current guidelines. This program will eventually include glucose-, lipid- and BP-lowering agents as needed and, when indicated, anti-platelet drugs. For ethical reasons, drugs will be also adjusted throughout the study to attain target levels and to account for reduced needs. The treatment regimen will include also a dietary prescription, which will be preceded by a preliminary nutritional evaluation with assessment of BMI and the individual patient requirements and preferences. The diet will contain 55% calories from complex carbohydrates, 30% from fat, and 15% from protein. Since all patients are overweight or obese, they will receive a low calorie diet (negative balance of 500 kcal/day, not <1500 Kcal in males and 1200 Kcal in females), calculated by adding the estimated energy expenditure from non-conditioning or non-volunteer and conditioning or volunteer physical activity to basal metabolism estimated using the gas exchange analyzer FitMate (Cosmed, Rome, Italy). Baseline LTPA will be calculated by multiplying the weekly hours spent in the various activities, as reported in the Minnesota LTPA questionnaire, by the metabolic equivalent (MET) score of each activity, and expressed as METs· h–1 · week–1. Patients will be also given a diary to be filled in daily with type of physical activity performed and time spent in each of them (Figure 2 and Table 4). Finally, patients will receive a list of intermediate, group B biochemical measurements, to be performed at each center laboratory immediately before the next visit (Table 3), will be prescribed.

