# **Treatments**

***Exercise program***

The training program for the EXE group consists of twice a week supervised sessions of 75 min duration of mixed (aerobic and resistance) exercise, for 12 months.

Aerobic training will be performed using treadmill, step, elliptical, arm or cycle-ergometer. Transformation of maximal oxygen consumption (VO2max)in exercise load will be performed by the use of a software (Wellness System, Technogym SPA, Gambettola, Italy) or a dedicated spreadsheet, which allow calculation of the individual training load for each equipment from VO2max using the American College of Sports Medicine (ACSM) equations [21].

Resistance training will consist of 4 resistance exercises, i.e. thrust movement on the transverse plane (chest press or equivalent), traction movement on the frontal plane (lateral pull down or equivalent), squat movement (leg press or equivalent), trunk flexion for the abdominals, and three stretching positions. Intensity will be adjusted according to improvements in predicted VO2max and 1RM, as recorded throughout the study, thus resulting in further increments of working loads. In addition, caloric expenditure will be increased progressively by 0.1 kcal/kg body weight/session every month (Table 5).

Subjects in the EXE group will be allocated to either moderate-intensity aerobic (at 55% of predicted VO2max) and resistance (at 60% of predicted 1 Repetition Maximum, RM) or high-intensity aerobic (at 70 % of predicted VO2max) and resistance (at 80% of predicted 1RM) exercise, depending on the centres, which have been preliminary assigned to exercise patients at moderate- or high-intensity. Exercise and duration of aerobic training and number of series will be managed to obtain the same caloric expenditure per kg body weight, independent of the intensity level of exercise.

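### For patients on heart-rate-affecting drugs the protocol changes only the stopping rule of the fitness test, not how VO2max is obtained, so tests before and after a change in drug status are not comparable

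*Protocol*

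**What the plan says.** Under Assessment of physical fitness (Cardio-respiratory fitness), the Protocol specifies a submaximal treadmill test with direct gas analysis, ended "at 80% of the predicted maximal heart rate (MHR = 220 – age"). The reason given for not testing to the maximum is that "heart rate varies linearly with VO2 to the point of maximum exertion, thus allowing extrapolation of the actual VO2max value".

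For patients on drugs that affect heart rate, a perceived-exertion scale takes over: "Patients will be stopped at the perceived value of 5-6 (hard) because, according to ACSM’s guidelines, this value corresponds to a heart rate of 70-89" per cent. The section gives these patients no other maximal heart rate, extrapolation or estimation method.

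Both arms are tested at baseline and at the end. The exercise arm is also tested every three months with gas analysis and monthly without it. Each step beyond the previous test adds 2 ml to predicted VO2max, and the load is raised accordingly.

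Four other places depend on this measurement or affect it:

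- Recruitment, randomization and baseline evaluation (visit R3): the regimen includes BP-lowering agents, and "drugs will be also adjusted throughout the study to attain target levels and to account for reduced needs".
- Exercise program: software or a spreadsheet is used, "which allow calculation of the individual training load for each equipment from VO2max", with aerobic targets of 55% or 70% of predicted VO2max depending on the centre.
- Secondary outcomes: the exploratory goals include "Relationship between physical fitness at baseline and during the study and modifiable cardiovascular risk factors".
- Statistical analysis plan (section of the Protocol): an ANOVA trend test relates fitness variation to risk factors. The regression that accounts for medication uses baseline treatment and treatment initiation as yes/no terms and ignores dose. It is not said to apply to the trend test.

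**The concern.** The protocol recognises that heart rate cannot end the test in these patients, yet heart rate remains the only stated basis of the estimate. A drug that lowers heart rate at a given workload moves the heart rate-VO2 line down. The line then meets an unmedicated age-predicted maximum at a VO2 the patient cannot reach.

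The two groups are also stopped differently, one at a single point and the other within a band. A patient who starts or comes off such a drug between tests is measured once under each rule. The difference between those tests mixes fitness with the drug change, and BP, one of the risk factors analysed, can respond to the same drug.

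At stake are the exploratory fitness analyses and, in the exercise arm, the derivation of the training load. The randomised HbA1c comparison does not use VO2max.

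**Working it through.** **1. Is 220 minus age the ceiling of the extrapolation?** The formula is not printed, but the protocol's own 2 ml per step offers a check.

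- Table 7 walking equation: one 1% step at 4.3 km/h (Table 6) costs 4.3 × 1000/60 × 0.01 × 1.8 = 1.29 ml/kg/min.
- Age 60, predicted maximum 160, stop at 128, resting rate 70 (assumed): the stop lies at (128 − 70)/(160 − 70) = 0.644 of the range.
- Extrapolated to 160, one step is worth 1.29/0.644 = 2.00 ml. For ages 45-75 and resting rates 60-80 the range is 1.85-2.33.
- Simple division by 0.80 gives 1.29/0.80 = 1.61, which also rounds to 2.

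The 2 ml increment therefore fits heart-rate extrapolation to 220 minus age but does not prove it. It also says nothing specific about medicated patients.

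**2. Reading A: the same extrapolation is used for medicated patients.** All inputs except 220 minus age are assumptions: age 60, true VO2max 22 ml/kg/min, resting VO2 3.5, resting rate lowered by 10 bpm to 65, and maximal rate lowered by 10%, 15% or 20% from 160.

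Estimate = 3.5 + (22 − 3.5) × (160 − 65)/(drug-lowered maximum − 65)

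| Maximal rate on drug | Estimate (ml/kg/min) | Ratio to true value |
| --- | --- | --- |
| 144 | 3.5 + 1757.5/79 = 25.7 | 1.17 |
| 136 | 3.5 + 1757.5/71 = 28.3 | 1.28 |
| 128 | 3.5 + 1757.5/63 = 31.4 | 1.43 |

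A change in drug status with fitness unchanged would move the estimate by 25.7 − 22 = 3.7 to 31.4 − 22 = 9.4 ml. For scale, the protocol credits 2 ml per step.

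Sensitivity: true VO2max 22, undrugged resting rate 70, ages 45-75, reductions of 5-25%, and the drug effect modelled as proportional, as a constant shift, or as a flatter slope only. The error runs from +4% (slope only, 5%) to +54% (proportional, 25%, age 75) and is upward in every variant.

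**3. Reading B: measured VO2 at the Borg stop is scaled as if it were 80%.** If the true fraction lies anywhere in 70-89%, the estimate is 70/80 = 0.875 to 89/80 = 1.11 of the true value. The error is about -12% to +11%, with no systematic overestimate.

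**4. Consequence for load, under Reading A only.** A nominal 55% becomes 0.55 × 1.17 = 64% to 0.55 × 1.43 = 78% of true VO2max. A nominal 70% becomes 0.70 × 1.17 = 82% to 0.70 × 1.43 = 100%. Table 5 fixes energy per session per kg, so intensity is affected and planned volume is not.

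**The case against.** The best defence is that 220 minus age is printed to define the 80% stop, not as an extrapolation ceiling for medicated patients. The protocol ties Borg 5-6 to a heart-rate percentage, so VO2 at the stop could be scaled as a submaximal fraction. That gives Reading B, a smaller and roughly symmetric error. This stands: the overestimate is conditional. It does not remove the point, because neither method is stated for these patients and under both they are measured differently from the rest.

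A reader might infer two stronger claims that the documents do not support.

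- **That patients on these drugs will train at up to 100% of their true VO2max.** That figure combines Reading A with a drug effect the documents do not give. Sessions are supervised, severe cardiovascular disease and angina are exclusions, and the monthly update follows steps reached rather than heart rate.
- **That the plan creates a spurious relation between fitness and risk factors.** The sign is not determined. If a drug is withdrawn because BP improved, estimated fitness falls while BP improves, which would mask a true relation. The protocol does not single out heart-rate-affecting drugs among those adjusted, and it gives neither the share of patients taking them nor the share expected to change.

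It is also fair that the secondary goals are described as exploratory.

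**Conclusion.** The point holds as a gap in measurement that affects the exploratory fitness analyses. For patients on heart-rate-affecting drugs the protocol changes the stop and gives no matching way to obtain VO2max.

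If the general extrapolation is applied, the estimate is too high. The direction is firm under that reading. The size, about +17% to +43% in the worked example, rests on assumed drug effects. If the stop is scaled as 80%, the error is about -12% to +11%.

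Under either reading, a patient whose drug status changes has tests under two rules, so part of that patient's fitness variation reflects the drug. How far this distorts the trend test, and in which direction, cannot be determined from the documents. The primary HbA1c comparison and its sample size are unaffected.

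**What to change.** - In the cardio-respiratory fitness section, state that VO2max extrapolated to 220 minus age is not treated as comparable for patients on heart-rate-affecting drugs.
- Flag drug status at each fitness test. Changes in therapy are already registered in the database (Follow-up and final evaluation), so this needs no new data collection.
- Repeat the fitness and fitness-variation analyses twice: excluding patients whose status changed between tests, and excluding all patients on such drugs. The second also covers dose changes, which a yes/no flag misses.
- Reconcile the R3 treatment text, the Exercise program section and the fitness-test section on how the training load is derived for these patients. The sponsor's clinicians decide how.

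Two alternatives are less suitable. Using directly measured submaximal VO2 for this group alone would mix two fitness metrics in one analysis. Requiring the same Borg stop at both tests cannot work for a patient who starts a drug after a baseline test that ended at 80%.

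The cost is a few sentences and two sensitivity analyses. The downside is fewer patients in those analyses.

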***Assessment of physical activity***

Prospective assessment of the volume of non-supervised physical activity throughout the study will be accomplished by the use of a diary in which patients will report daily the type(s) of physical activity performed and the time spent in each of them (Figure 2). This diary is based on the range of physical activities considered in the Minnesota Leisure-LTPA questionnaire (Table 4). These activities will be divided in conditioning or volunteer (corresponding to LTPA) and non-conditioning or non-volunteer (including commuting, occupational and home activities) [24]. Volume will be calculated by multiplying the METscores corresponding to each Minnesota code [25], by time in hours per week spent in each activity, and expressed as METs . h-1 .week-1.

For supervised aerobic exercise, energy expenditure during supervised sessions will be calculated automatically by the machines from workload (i.e. the combination of speed and slope for treadmill, steps per minute for step and power for ergometer), using the ACSM’s equations [21] (Table 7). For supervised resistance exercise, since direct measurements in patients with low physical fitness such as T2DM subjects ([name] et al., unpublished results) did not confirm that energy expenditure varies with training intensity [25], we have decided on a conservative estimate of 3 METs/hour.

***Assessment of cardiovascular risk factors***

Clinical and laboratory data will be evaluated at baseline and at the end of the study, for assessing the effect of lifestyle intervention, and also at 3, 6 and 9 months, in order to verify the adequacy of treatment regimen. Clinical parameters include body height and weight, with calculation of BMI, waist circumference and BP. Laboratory parameters include Group A biochemical measurements, to be performed at central laboratory (Laboratory of Clinical Chemistry, Sant’Andrea Hospital, Rome, Italy) and Group B biochemical measurements, to be performed in each center laboratory (Table 3).

***Assessment of costs***

Costs will be calculated using standard unit costs of the resources used, averaged on the year 2006 costs of resources in Italy (tables produced by Italian National Institute of Statistics). Cost analysis includes direct medical costs and direct and indirect social costs and is reported in U.S. dollars per capita per year, adjusted to year 2006, as previously reported [4].

*Direct medical costs*. These costs include expenses for medications and other costs usually paid by the National Health Service, including counseling intervention, laboratory testing, hospitalization, and outpatient care.

*Social costs.* Direct social costs include the value of the time that participants spend in practicing physical activity, cost of related items, transportation to exercise places, and admission to health clubs, whereas indirect social costs include time that participants report as lost from work or usual activities as a result of counseling visits, illness, or injury.

**Statistical analysis**

***Sample size calculation***

Sample size calculation will be based on the mean HbA1c values (7.6±1.6 %) detected in the SFIDA population, consisting of 11,000 type 2 diabetic patients, aged 46-69 years, a HbA1c reduction of at least 0.5 % in EXE vs. CON group and a statistical power of 90% (α=0.05). To this end, 215 patients per arm need to be enrolled (430 patients total). Assuming a dropout rate of up to 25%, we will recruit 600 patients. Such a sample size also guarantees a statistical power of >90% to detect changes indicated for each of the parameters in the secondary endpoints.

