***Statistical analysis plan***

The c2 test for categorical variables and the Student’s t test or the corresponding nonparametric Mann-Whitney test for continuous variables will be utilized to compare patients’ characteristics at baseline. The efficacy of intervention on primary and secondary endpoints will be assessed using the unpaired t-test or the Mann Whitney U test for continuous variables, by comparing between-groups changes from baseline to end-of-study. For categorical variables (i.e. medications), logistic regression analysis will be applied, with end-of-study rate of use included in the model as the dependent variable and baseline rate of use and study arm included as covariates.

To account for change in medication throughout the 12-month period, multiple regression analysis will be performed, with baseline-to-end-of-study changes as dependent variable and treatment at baseline and treatment initiation during the study as dichotomous variables (yes versus no), whereas drug dosage will not be taken into consideration.

Within group end-of-study vs. baseline values will be compared using the McNemar test for categorical variables and the Wilcoxon signed ranks test for continuous variables. To identify independent predictors of HbA1c changes from baseline, a multiple regression analysis was applied, with mean value of METs, baseline HbA1c values, gender, age, and changes in HOMA-IR, BMI, waist, total, LDL-cholesterol and HDL-cholesterol, and hs-CRP as covariates forced in the model.

Multivariate analysis techniques (multiple or logistic regression) will be used to adjust for differences in the distribution of one or more parameters between the two arms, whereas the ANOVA trend test will be applied for evaluating the relationship of volume and intensity of exercise training (dose/response) and fitness variation with modifiable cardiovascular risk factors.

The likelihood to achieve glycaemic and nonglycaemic targets after 12 months will be estimated using logistic regression, adjusted for baseline status (on-target vs. not-on-target).

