b VITROS 5,1 FS Chemistry System (Ortho-Clinical Diagnostics, Inc, Raritan, NJ, USA)

c Chemiluminiscent immunometric assays (Immulite 2000 Thes; Diagnostic Products Corporation, Los Angeles, CA, USA)

dmAlb VITROS (Ortho-Clinical Diagnostics, Inc)

***Group B***– to be performed in each centre laboratory at 3, 6 an 9 months.

- HbA1c and blood glucose levels;
- serum triglycerides and total and HDL cholesterol levels with LDL cholesterol calculation;
- BUN, serum creatinine, urinalysis, uric acid (if present hypeuricemia);
- serum aspartate aminotransferase, alanine aminotransferase, -glutamyl-transpeptidase and creatine phosphokinase levels (if treated with statins);
- plasma sodium and potassium levels (if treated with BP-lowering agents).

**Table 4:** List of Physical Activities (in Italian) and the relative METs intensities utilized to predict the accumulated volume of physical activity (METs·h-1·wk-1). Activities included and corresponding METS values are derived from the Minnesota Leisure Time Physical Activity Questionnaire.

| **PHYSICAL ACTIVITY** | **METS** |
| --- | --- |

1 Passeggiare 3.5

2 Camminare da casa al lavoro o nella pausa lavoro 4.0

3 Camminare (portando un carrello con la spesa) 3.5

4 Camminare (portando le sporte della spesa) 5.5

5 Salire le scale 8.0

6 Camminare in campagna/traking 6.07

7 Escursioni con lo zaino 7.0

8 Scalate in montagna 8.0

9 Andare in bicicletta al lavoro 4.0

10 Ballo 4.5

11 Aerobica o balletto 6.0

12 Giocare con i bambini 4.5

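### Up to 25% dropout is met only by extra recruitment; the primary test needs a 12-month HbA1c, so response-related dropout that differs by arm can bias the effect either way

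*Protocol*

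**What the plan says.** - **Dropout (Protocol, Sample size calculation).** The requirement is "215 patients per arm need to be enrolled (430 patients total"), based on "mean HbA1c values (7.6±1.6 %) detected in the SFIDA population", "a HbA1c reduction of at least 0.5 % in EXE vs. CON group" and "a statistical power of 90% (α=0.05"). Dropout is then handled in one sentence: "Assuming a dropout rate of up to 25%, we will recruit 600 patients".
- **Primary test (Protocol, Statistical analysis plan).** Continuous endpoints are assessed with a two-sample t-test or a Mann-Whitney test, "by comparing between-groups changes from baseline to end-of-study". None of the regressions listed after it uses HbA1c from an intermediate visit.
- **Interim HbA1c (Protocol, Table 3, Group B).** HbA1c is among the measurements "to be performed in each centre laboratory at 3, 6 an 9 months". Under Assessment of cardiovascular risk factors, the baseline and final values serve to judge the intervention; the interim values serve to check that treatment is adequate.
- **Final HbA1c (Protocol, Follow-up and final evaluation).** Visit F4 is scheduled for the patients recruited, with a blood sample sent to the central laboratory.

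**The concern.** Recruiting more patients replaces lost numbers. It does not make those who remain representative of those randomised. A change score exists only where there is a final value, so the named test works on whoever reaches F4 unless something else is specified.

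The two arms ask very different things of patients. Under Exercise program, EXE attends two supervised 75-minute sessions a week for a year, with caloric expenditure that rises every month (Table 5). CON has conventional care with counseling. In an open trial of this kind, both the rate of leaving and the reasons for it can plausibly differ by arm. If leaving is also related to HbA1c response, the comparison of completers no longer estimates the effect in the randomised population. Three interim HbA1c values that could carry information on the missing outcomes are collected but play no part in the efficacy analysis.

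**Working it through.** **1. The plan's own figures.** Inputs from Sample size calculation: difference 0.5, SD 1.6, alpha 0.05 (taken as two-sided), power 90%.

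n per arm = 2 × (1.96 + 1.282)² × 1.6² / 0.5² = 216 after rounding up, against 215 stated. This reproduces; 215 per arm gives 90.0% power.

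Dropout: 430 / (1 − 0.25) = 574, below the 600 planned. At 25% loss, 600 × 0.75 = 450, or 225 per arm, with 91% power. The allowance does its job for power. The number without a final value could reach 600 × 0.25 = 150.

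**2. What governs the bias.** Let d be the share of an arm that drops out, and g the amount by which the unseen HbA1c change of its dropouts is worse than that of its completers. The exaggeration of the benefit among completers is

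d(EXE) × g(EXE) − d(CON) × g(CON).

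The protocol gives neither d by arm nor g, so the values below are assumptions.

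| Assumption | g = 0.2 | g = 0.5 | g = 0.8 |
|---|---|---|---|
| 25% dropout in each arm, same gap in both | 0 | 0 | 0 |
| 25% EXE, 15% CON, same gap in both | 0.02 | 0.05 | 0.08 |
| 25% EXE, gap in EXE only | 0.05 | 0.125 | 0.20 |

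The last row is 10%, 25% and 40% of the 0.5 target. With no true effect, 225 per arm and SD 1.6, the standard error is 1.6 × √(2/225) = 0.151, and the two-sided type I error would be 6.3%, 13.2% and 26.4%. If the gap lies in CON only, the signs reverse.

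**3. Simulation.** Assumptions, none of them from the protocol except the SD of 1.6, the size of the effect and the 25%: true 12-month effect −0.50; 6-month effect −0.25; equal correlation of 0.5 to 0.7 between baseline, 6 and 12 months; 25% dropout per arm; where dropout depends on response, its log-odds rise by 0.4 to 0.8 per point of 6-month HbA1c change, so poorer responders leave more often.

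| Dropout depends on response in | Completers' difference in change | Relative to −0.50 |
|---|---|---|
| EXE only | about −0.58 to −0.71 | overstated by 16% to 42% |
| both arms alike | about −0.50 | none |
| CON only | about −0.30 to −0.43 | understated by 14% to 40% |

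Repeat runs move these figures by about 0.01. Imputing the missing 12-month value within arm from baseline and 6-month HbA1c returns about −0.50. That is expected by construction, because dropout was generated from the 6-month value used to impute. It shows what the method does when its assumption holds, not that the assumption holds here.

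**The case against.** **A separate analysis plan may deal with this.** The protocol nowhere says that only patients with a final value are analysed, and a two-sample test on changes is compatible with imputed final values. That stands in part: the absence of a named analysis set or missing-data rule is not by itself the finding. The point rests on what the protocol does fix, namely the test, the quantity tested, the sole response to dropout and a limited role for the interim HbA1c. Followed as written, these amount to a completers analysis.

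**Nothing shows that the effect is inflated.** A reader might infer that poor responders will leave EXE and exaggerate the benefit. The protocol does not say which arm will lose patients or that leavers respond poorly, and the calculations give no bias or the opposite bias under equally simple assumptions. This objection stands in full.

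**The sample size is sound.** If a quarter of EXE stopped with no benefit while completers gained 0.50, the effect over all randomised patients would be 0.75 × 0.50 = 0.375, with 82% power at 300 per arm fully followed. A reader might take this as showing the plan has 82% power, not 90%. It does not: the zero benefit is an assumption, and the 82% belongs to a different analysis of a diluted effect.

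**Stopping sessions is not the same as missing F4.** No text ends visits when exercise stops, so 150 is a planning ceiling. That also stands.

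**Interim HbA1c is imperfect.** It comes from each centre's own laboratory, therapy is changed in response to it, and anyone leaving before F1 has none. This rules out substituting it for the final value, but not using it as auxiliary information.

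**Conclusion.** The concern holds as a risk of bias of unknown sign. The dropout allowance secures power (91% at 225 per arm) and does nothing for validity. Up to 150 of 600 randomised patients could be missing from the primary comparison, and the interim HbA1c that could inform their outcomes is not used for efficacy.

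Under the stated assumptions, a true effect of −0.50 could appear as anything from about −0.30 to −0.71, depending on the arm in which dropout is related to response, and would be unbiased if both arms behaved alike. These are illustrations and not forecasts; they depend on an assumed dropout mechanism, correlation and 6-month effect. The documents do not support saying that the effect will be inflated or that 215 per arm or 600 in total is miscalculated. The change is worth making because it is cheap and removes a foreseeable weakness in the primary result.

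**What to change.** 1. Name all randomised patients, in their assigned arm, as the primary analysis set.
2. State that the F4 central HbA1c is obtained whether or not a patient is still attending sessions. F4 is already scheduled, so this is a clarification.
3. Handle missing F4 HbA1c by multiple imputation within arm from baseline HbA1c, F1 to F3 HbA1c and the stratification factors (centre, age group, type of diabetes treatment). Use the F1 to F3 values only as auxiliary variables, because they are local assays; do not carry them forward as the outcome.
4. Add a not-missing-at-random sensitivity analysis, for example reference-based imputation in which missing EXE outcomes are drawn from the CON pattern.
5. Report dropout and its reasons by arm.

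The cost is a few sentences of text and modest programming, with no change to the sample size. The estimate may turn out less favourable or less precise than the completers' figure.
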